### Primary outcome

The Western Ontario McMaster University Osteoarthritis Index (WOMAC) pain score is the primary outcome. WOMAC is a disease-specific quality of life questionnaire for use in osteoarthritis clinical trials [59]. The WOMAC pain subscale has 5 items, with the rating scale ranging from 0 (none) to 4 (extreme), with higher scores indicating worse painful conditions [60].

### Secondary outcomes

#### Evaluation of the severity of osteoarthritis

The Lequesne Algofunctional Index and the WOMAC are commonly used instruments to assess pain, physical disability, and disease severity in patients diagnosed with OA [61]. Studies previously conducted show that WOMAC and the Lequesne Functional Something Index have a good correlation. Bellamy et al. [60] demonstrated that the questionnaires show similar results when used to record improvement of patients with OA submitted to medication.

According to Samuel and Kanimozhi [59] when analyzing the results used in the diagnosis, prognosis, and rehabilitation of patients with knee OA, the WOMAC, and the Lequesne Algofunctional Index in the pain subscale shows reliability and a good correlation of results. However, although both address the severity of OA and the physical function of these patients, the questionnaires are not a substitute for assessing the symptoms and disabilities of these cases [62].

#### Functional assessment and risk of falls

The Time Get Up and Go Test (TUG), 30-second Chair Stand Test (30-sCST), and 40-m Fast Paced Walk Test (40mFPWT) are tests recommended by the Osteoarthritis Research Society International (OARSI), considered as a basic set of functional tests for assessing physical performance in patients with knee OA [63]. All three tests (TUG, 30-sCST, and 40mFPWT) are also used to assess balance and risk of falls [64, 65], mainly due to their having good to excellent correlation with poor balance and number of falls [66, 67]. The tests will be applied according to the protocol described by OARSI [63]. For TUG and 40mFPWT, tests completed in less time are associated with better fitness and lower risk of falling [64, 66]. For 30-sCST, a higher number of repetitions indicates better functional prognosis [67].

#### Level of physical activity

The level of physical activity will be verified using the Brazilian version of the International Physical Activity Questionnaire (IPAQ), long version. This questionnaire includes 27 questions about physical activities performed in a regular week, with vigorous, moderate, and light intensity, with a minimum duration of 10 continuous minutes, distributed in five domains: work, transportation, domestic activity, leisure/recreation and sitting. The level of physical activity will be classified continuously by calculating the estimated energy expenditure in METs (metabolic equivalent) [69].

#### Evaluation of muscle strength of knee extensors

The muscle strength of the knee extensors will be performed using the MicroFET2® manual dynamometer (Hogan Scientific - USA), which is a reliable and valid portable device for the evaluation of the isometric muscle strength and power of lower limbs [70]. The procedures for collecting the isometric strength of knee extensors will follow the steps of an already published study [71].

#### Quality of life assessment

The Brazilian version of the generic questionnaire of quality of life RAND 36-Item Short-Form Survey (SF-36) Version (1.0) [72] will be applied, which evaluates 8 domains, namely: functional capacity, limitation due to physical aspects, pain, general health, vitality, social aspects, emotional aspects, and mental health. The questionnaire score is given by domain and ranges from 0 to 100, in which the highest score reflects the best function.

#### Pain immediately after training

Knee joint pain during exercise will be assessed in all sessions (immediately after each set) by the pain VAS. Participants will be asked to report their knee pain score before starting interventions and immediately at the end of each session. The final score will be the difference between the first and second score.

#### Global Perceived Effect scale

For this research, the Global Perceived Effect Scale (GPE) scale was adapted to assess the patient perception of recovery from the first session and will be applied during all follow-up points. The guiding question was “Compared to the day you started the treatment, how do you describe your knee pain today?” It is a numerical scale of 11 points (− 5 to 5), with − 5 being much worse; 0 being no change; and 5 being complete recovery. The higher the score, the better the recovery from the condition [73].

### Sample size calculation

Sample size is based on detecting non-inferiority of the groups that will receive interventions with BFR compared to active placebo with exercise. For the change in pain on the WOMAC subscale (score 0–20), a non-inferiority margin (NIM) of 2.1 units was chosen as it is less than the minimal clinically important difference (MCID) reported as 2.4 points in the WOMAC questionnaire [74]. The margin of 2.1 units is the same of 11% of the total WOMAC pain subscale score, which is higher than the 8–9% commonly used in previous studies [75–77].

Assuming a standard deviation (SD) of 3.14 [78], 80% power at an alpha level of 5% to the primary measuring point 72 h after completion of interventions and a drop-out of 15%, we will need 33 participants per group, resulting in a total sample of 165 participants. The use of bilateral alpha value is in accordance with the recommendations of not ignoring superiority in non-inferiority trials [79, 80]. The sample size calculation was performed using the R software version 4.1.2.

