### Randomization

Participants will be randomly allocated in the equal ratio between groups (1:1:1:1:1) using the generator available at www.randomization.com by a researcher ([name]) who will not be aware of the research group participants and evaluations. Balanced permutations in blocks will be used in relation to the presence of unilateral or bilateral knee OA.

The allocation of participants will be hidden in opaque numbered and sequentially sealed envelopes, prepared before the study by a researcher ([name]) who did not participate in the recruitment and assignment of the groups. The corresponding envelopes will be opened once the participants enrolled have completed all baseline assessments.

The researcher responsible for evaluations ([name]) and data analysis ([name]) will be blind to the groups of participants. The order of the evaluations will follow a predetermined sequence that will try to reduce the interference of the physical fatigue of a test in its successor:
Set 1: WOMAC, MMSE, and LOP;Set 2: IPAQ, Time Get Up and Go Test (TUG) and 30-second Chair Stand Test (30-sCST);Set 3: SF-36, Lequesne and isometric strength evaluation of the knee extensors;Set 4: Clinical Test of Sensory Interaction and Modified Balance, 40-m Fast Paced Walk Test (40mFPWT), Demographic Data and 7-10 RM test.

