### Statistical analysis

The statistical analysis will be conducted following the principles of intention-to-treat analysis. The normality distributions of the data will be assessed by visual inspection of histograms. In order to ensure data quality and data consistency between the source data and the data entered into the database, the data will be entered using the double entry method by two researchers ([name] and [name]) independently into the database.

A linear mixed-effects model will be used to examine the between-group differences (BFR40% + rest, BFR80% + rest, BFR40% + LL, BFR80% + LL, and HIRE+placebo), time (baseline, 72 h, 20, 28, 40, 52, and 64 weeks), and group-time interaction in the primary outcome of pain intensity (measured using WOMAC subscale), and secondary outcomes of the disease severity, physical functional data, balance data, quality of life, pain during intervention, global perceived effect scale, and muscle strength. The 72-h follow-up will be the primary measurement point, and the other timepoints will be used to support the understanding of the effects of the interventions. Non-inferiority will be demonstrated if the lower limit of the 95% bilateral confidence intervals (CI) for the difference between the HIRE and each BFR group is above − 2.1 units for change in the WOMAC pain subscale. The comparison between the BFRs groups and the secondary results will be interpreted using the superiority framework since we have not pre-defined any NIMs for these outcomes.

Analyses will be adjusted for baseline demographic and clinical characteristics of age, sex, disease severity, BMI, and educational level, considering 80% power at an alpha level of 5%. The effect sizes (Cohen’s *d*) of the analyses will be presented with their respective 95% CIs. Chi-square tests will be used to test for possible differences in the adverse events observed between groups. All analyses will be calculated by one of the authors ([name]) blinded to the allocation of groups, using tables with randomization codes. The statistical analysis will be conducted using the SPSS 25.0 software (SPSS, Chicago, IL, USA).

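### The 33 per arm fits a one-sided 5% test, but the protocol states a two-sided 5% alpha and a 95% CI rule, under which power is about 70%, not 80%

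*Protocol article*

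**What the plan says.** In the protocol article, the section Sample size calculation gives these inputs:

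- margin: "a non-inferiority margin (NIM) of 2.1 units was chosen", on a 0–20 pain subscale and described for the change in pain;
- variability: "Assuming a standard deviation (SD) of 3.14";
- error rates: "80% power at an alpha level of 5% to the primary measuring point 72 h after completion of interventions";
- attrition: "a drop-out of 15"%.

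From these it concludes that "we will need 33 participants per group, resulting in a total sample of 165 participants". On sidedness it adds: "The use of bilateral alpha value is in accordance with the recommendations of not ignoring superiority in non-inferiority trials".

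The section Statistical analysis sets the decision rule: "Non-inferiority will be demonstrated if the lower limit of the 95% bilateral confidence intervals (CI") for HIRE against each BFR arm lies above −2.1. The same section repeats the 80% power and 5% alpha. The section Randomization gives equal allocation to the five arms. The abstract confines the non-inferiority framework to the primary outcome, comparing HIRE with each BFR arm, so the powered comparison is pairwise.

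**The concern.** Comparing one limit of a two-sided 95% interval with a margin is a one-sided test at 2.5%. The two-sided alpha in the sample size section and the interval rule in the analysis section therefore agree with each other. The number of participants agrees with neither: 33 per arm is what the stated margin, SD, power and drop-out give at one-sided 5%.

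The mismatch affects all four HIRE-versus-BFR comparisons, which are the primary objective. If a BFR arm fails to show non-inferiority, readers will weigh that failure as coming from a trial with a 20% chance of missing true equality. On the protocol's own inputs the chance is about 30%. An uncorrected mismatch also leaves room to argue later for a 90% interval, because that is the rule the 33 fits.

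**Working it through.** **Inputs.** Margin Δ = 2.1, SD σ = 3.14, power 80% (z = 0.8416) and drop-out 15%, all from Sample size calculation; 1:1 within each pair, from Randomization. The true difference is taken as 0. The protocol states none, so this is the conventional assumption.

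**Formula.** Evaluable per arm: n = 2(z_α + 0.8416)² σ² / Δ². Here 2σ²/Δ² = 2 × 9.8596 / 4.41 = 4.471.

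**Reproducing the stated figure (one-sided 5%, z_α = 1.645).** n = 4.471 × 2.4866² = 27.6, so 28 evaluable. Then 28/0.85 = 32.9, so 33 per arm, and 5 × 33 = 165. This matches the protocol.

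**Using the stated rule (2.5% per side, z_α = 1.960).** n = 4.471 × 2.8016² = 35.1, so 36 evaluable.

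- Rounding at each step: 36/0.85 = 42.4, so 43 per arm, 215 in total.
- Rounding once at the end: 35.1/0.85 = 41.3, so 42 per arm, 210 in total.
- With the noncentral t distribution: 37 evaluable, and 37/0.85 = 43.5, so 44 per arm.

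The gap from 33 is at least 9 per arm, so neither rounding nor the drop-out formula explains it.

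**Power of the planned size under the 95% interval rule.** Power = Φ(Δ/SE − 1.96), with SE = σ√(2/n).

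- 28 evaluable: SE = 3.14 × √(2/28) = 0.839; 2.1/0.839 − 1.96 = 0.542; Φ(0.542) = 70.6%.
- 33 evaluable (no drop-out): Φ(0.757) = 77.5%.

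| Evaluable per arm | One-sided 5%, normal | 95% CI rule, normal | 95% CI rule, two-sample t |
|---|---|---|---|
| 28 | 80.4% | 70.6% | 69.1% |
| 33 | 85.8% | 77.5% | 76.3% |

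With 28 per arm and the error variance pooled over all five arms, the t-based figure is 70.0%.

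**Other routes to 33.** Replacing the margin by the 2.4-point minimal clinically important difference, at 2.5% per side, gives 27 evaluable and 32 per arm (normal), or 28 evaluable and 33 per arm (t). Reading the margin as 2.2 (11% of 20) gives 38 or 39 per arm. With the margin held at 2.1, no calculation at 2.5% per side gives fewer than 42.

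**The case against.** Four points can be made for the protocol.

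1. **The cause is inferred.** The 2.4-point route also reaches 33 at the claimed two-sided alpha, so the document cannot settle whether the slip was in the alpha or in the margin. That stands as a caution about the cause. It does not rescue the figure, because both the sample size section and the decision rule use 2.1.

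2. **The analysis is adjusted.** The mixed model includes baseline as a time point and adjusts for age, sex, disease severity, BMI and education. If 3.14 is an unadjusted SD, so that the residual SD is 3.14√(1 − r²), a baseline correlation r of 0.3, 0.4, 0.45 or 0.5 gives power of 75%, 78%, 80% or 82% with 28 per arm. This is a real possibility, but the calculation claims no such gain and states no correlation. The section also frames the margin for change. If 3.14 is already the SD of change, the stated inputs give 70.6%. If it is a raw-score SD and simple change is analysed, the SD is 3.14√(2(1 − r)) and a correlation of 0.4 gives only 63%.

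3. **Twenty-eight evaluable is the planned floor.** The eligibility section invites participants who stop attending to the follow-up assessments and says losses should not exceed 15%. Better retention helps, but full retention still leaves power at 77.5%.

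4. **Validity is untouched.** The decision rule is clear, and the error does not raise the chance of a false non-inferiority claim. That is correct: the fault lies in the stated power, not in the rule.

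**Conclusion.** The concern holds. The stated 33 per arm does not follow from the stated margin, SD, power, drop-out and two-sided alpha; it follows from the same inputs at one-sided 5%. Under the 95% interval rule, power per comparison is about 70% with the planned drop-out and about 76–78% with none. The type II error at the planned drop-out is thus roughly 30%, half as large again as the 20% stated.

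These figures assume a true difference of zero, an SD of 3.14 for the analysed outcome, and no variance gain from covariates, since the protocol claims none. They apply to each comparison singly; the power to show non-inferiority for all four BFR arms is lower. The stated power of the primary analysis is wrong as written and must be corrected.

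**What to change.** Keep the two-sided 95% interval rule and correct the sample size section so that it says:

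- 33 randomised per arm (28 evaluable) gives about 70% power for each comparison, at a margin of 2.1, an SD of 3.14 and a true difference of zero;
- 80% power under the same rule would need 42–43 randomised per arm;
- whether 3.14 is the SD of the raw score, the change or the residual;
- if a gain from baseline adjustment is expected, the assumed correlation and the resulting power.

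The 80% power statement in the analysis section should be changed to match. The interval should not be narrowed to 90% afterwards to justify the number.

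The cost is a rewording and a less favourable power statement; no extra participants are required. Should the sponsor instead choose to keep 80% on these inputs, the total would rise from 165 to 210–215, which is 45–50 more participants.

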### Statistical analysis

The statistical analysis will be conducted following the principles of intention-to-treat analysis. The normality distributions of the data will be assessed by visual inspection of histograms. In order to ensure data quality and data consistency between the source data and the data entered into the database, the data will be entered using the double entry method by two researchers ([name] and [name]) independently into the database.

A linear mixed-effects model will be used to examine the between-group differences (BFR40% + rest, BFR80% + rest, BFR40% + LL, BFR80% + LL, and HIRE+placebo), time (baseline, 72 h, 20, 28, 40, 52, and 64 weeks), and group-time interaction in the primary outcome of pain intensity (measured using WOMAC subscale), and secondary outcomes of the disease severity, physical functional data, balance data, quality of life, pain during intervention, global perceived effect scale, and muscle strength. The 72-h follow-up will be the primary measurement point, and the other timepoints will be used to support the understanding of the effects of the interventions. Non-inferiority will be demonstrated if the lower limit of the 95% bilateral confidence intervals (CI) for the difference between the HIRE and each BFR group is above − 2.1 units for change in the WOMAC pain subscale. The comparison between the BFRs groups and the secondary results will be interpreted using the superiority framework since we have not pre-defined any NIMs for these outcomes.

Analyses will be adjusted for baseline demographic and clinical characteristics of age, sex, disease severity, BMI, and educational level, considering 80% power at an alpha level of 5%. The effect sizes (Cohen’s *d*) of the analyses will be presented with their respective 95% CIs. Chi-square tests will be used to test for possible differences in the adverse events observed between groups. All analyses will be calculated by one of the authors ([name]) blinded to the allocation of groups, using tables with randomization codes. The statistical analysis will be conducted using the SPSS 25.0 software (SPSS, Chicago, IL, USA).

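### On its natural reading the primary non-inferiority contrast is an unadjusted change-score comparison: valid, but less precise than a baseline-adjusted one that needs no new data

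*Protocol article*

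**What the plan says.** The Statistical analysis section specifies a linear mixed model with group, time and "group-time interaction in the primary outcome of pain intensity". Time has seven levels, and baseline is the first. Non-inferiority is read from the two-sided 95% confidence interval for the HIRE-versus-BFR difference in change in WOMAC pain, with 72 h as the primary time point.

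The adjustment is given as a list: "Analyses will be adjusted for baseline demographic and clinical characteristics of age, sex, disease severity, BMI, and educational level". Baseline WOMAC pain is not in it. The section does not say whether these covariates enter as main effects or also by time, and it does not set the baseline means equal across groups.

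The Randomization section says "Balanced permutations in blocks will be used in relation to the presence of unilateral or bilateral knee OA". That factor is not in the list either. The same section says that envelopes are opened only once all baseline assessments are complete, so baseline pain is measured before allocation is known.

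Under Sample size calculation, "a non-inferiority margin (NIM) of 2.1 units was chosen", with an SD of 3.14, "80% power at an alpha level of 5% to the primary measuring point 72 h after completion of interventions", 15% drop-out and 33 per group.

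**The concern.** When baseline is a response level and each group has its own baseline mean, the group-by-time contrast at 72 h is the difference between groups in mean change. In a randomised trial that estimate is unbiased, but it subtracts the whole of any chance baseline difference instead of the part that carries over to follow-up. It is therefore never more precise than a baseline-adjusted estimate and it shifts with chance imbalance. With about 33 per arm, such imbalance is to be expected. An imbalance in the HIRE arm enters all four non-inferiority comparisons, because they share that arm.

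The stated adjustment may look as if it deals with this. Whether it does depends on how the covariates enter the model.

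**Working it through.** **Inputs.** From the article: margin 2.1, SD 3.14, 33 per group, 15% drop-out (33 × 0.85 ≈ 28 evaluable), two-sided 95% interval. Not in the article, so assumed: correlation rho between baseline and 72-h pain, range 0.3 to 0.7, with equal SDs at the two times. The article does not say whether 3.14 is the SD of the score or of the change, so both readings are shown.

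**The plan's own figure.** n = 2 × (SD/margin)² × (z_alpha + z_power)², with (3.14/2.1)² = 2.236.
- One-sided 5%: 2 × 2.236 × (1.645 + 0.842)² = 27.6, so 28; 28/0.85 gives 33. This matches.
- Two-sided 5%, as the text describes: 2 × 2.236 × (1.960 + 0.842)² = 35.1, so 36; 36/0.85 gives 43. This does not match 33.

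Under the stated interval with 28 per arm, SE = 3.14 × √(2/28) = 0.839 and power = Φ(2.1/0.839 − 1.96) = 70.6%. This is the starting point when 3.14 is the SD of change.

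**Variance ratio.** With score SD s, the change score has variance 2s²(1 − rho) and the baseline-adjusted outcome has s²(1 − rho²). The ratio is (1 + rho)/2.

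**Power with 28 per arm and the two-sided 95% interval**

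| Assumed rho | Variance ratio | 3.14 = SD of change: before → after | 3.14 = SD of score: before → after |
|---|---|---|---|
| 0.3 | 0.65 | 70.6% → 87.4% | 56.2% → 74.6% |
| 0.5 | 0.75 | 70.6% → 82.4% | 70.6% → 82.4% |
| 0.7 | 0.85 | 70.6% → 77.5% | 89.8% → 93.9% |

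Example at rho 0.5: adjusted SE = 0.839 × √0.75 = 0.727, and Φ(2.1/0.727 − 1.96) = 82.4%. A simulation with 28 per arm gave an SE of 0.731.

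**What the listed covariates do.** Generalised least squares for five groups and seven times, rho 0.5, compound symmetry, 33 per arm, SE of the 72-h change contrast:
- no covariates: 0.773
- five time-constant covariates as main effects: 0.773
- stratum main effect added: 0.773
- common baseline mean, with the same main effects: 0.670

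With 5 of 33 per arm lost after baseline, the SE is 0.8232 without and 0.8233 with the covariates, and 0.728 with a common baseline mean.

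**If covariates enter by time.** With a severity score that correlates 0.6 with baseline pain (assumed), rho 0.5 and 28 per arm, the simulated SE falls from 0.839 to 0.806. That is part of the way to 0.731.

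**Chance imbalance.** If 3.14 is the score SD, the standard error of a baseline difference between two arms of 33 is 3.14 × √(2/33) = 0.77. At rho 0.5 a difference of that size shifts the change contrast by (1 − 0.5) × 0.77 ≈ 0.39 points, or 0.39/2.1 ≈ 18% of the margin.

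**The case against.** The strongest defence is that nothing here is an error. Baseline pain is in the model as a response and is subtracted out, the contrast is unbiased, and margin and decision rule are both defined on change. A full analysis plan, not shown, might constrain the baseline means or enter covariates by time. This stands in part: the issue is efficiency, not validity. But the article does state the model and an explicit covariate list, and a reader would fit free baseline means from it.

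Four stronger readings are tempting and are not supported.
- *That leaving out the stratum costs precision.* A stratum main effect cancels from the change contrast exactly as the listed covariates do. A gain needs the stratum to predict change and to enter by time, and the article gives no figure for that. What remains is a mismatch between design and analysis.
- *That the listed covariates cannot help.* This holds for main effects only. The article does not give the form, and disease severity may carry some baseline pain, since the section on severity of osteoarthritis names both Lequesne and WOMAC.
- *That power goes from 71% to 82%.* That is one point, rho 0.5, in an assumed range.
- *That the covariate list makes the trial underpowered.* The shortfall against 80% is a separate matter: 33 per group follows from a one-sided 5% test, while the text describes a bilateral alpha and a two-sided 95% interval. Under the score-SD reading with rho 0.7, power exceeds 80% without any adjustment.

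**Conclusion.** The point holds as an efficiency recommendation. As written, the primary contrast is most naturally an unadjusted change-score comparison. Baseline adjustment would cut its variance by 15% to 35% for rho from 0.7 down to 0.3. The gain in power is 7 to 17 percentage points if 3.14 is the SD of change and 4 to 18 if it is the SD of the score. The direction is the same throughout that range; the size rests on a correlation that the article does not give. The current analysis remains valid, and no power or coverage gain is claimed for the stratum.

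**What to change.** In the Statistical analysis section:
1. Constrain the baseline mean of WOMAC pain to be common to the five groups, so that groups differ only after baseline. This is preferred because it keeps every randomised participant with a baseline value, in line with the intention-to-treat statement under Eligibility criteria. The alternative is to model post-baseline WOMAC pain with baseline WOMAC pain by time as a covariate; that drops anyone without a post-baseline visit.
2. Enter the unilateral/bilateral stratum and the listed covariates with time interactions, so that they can act on the 72-h contrast.
3. Say which instrument disease severity means. If it is a WOMAC score that contains the pain items, it overlaps with the baseline response and should not also be a covariate in the common-baseline model.
4. Take the HIRE-versus-BFR contrast at 72 h from this model. The quantity estimated is still the group difference in change, so the 2.1-point margin applies unchanged.
5. Do the same for secondary outcomes that have a baseline value.

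The cost is a change of wording and a few degrees of freedom. All variables are already collected.

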The BFR has shown promising results in musculoskeletal rehabilitation. It consists of a momentary and controlled mechanical compression of the proximal segment of the limb [25]. The most accepted mechanisms that can explain the development of muscle hypertrophy in BFR is the accumulation of metabolites around the trained muscle as an adaptive response to local hypoxemia [26, 27].

The effectiveness of BFR in patients with knee OA is comparable to traditional protocols for gaining muscle strength in knee muscle extensors [28–30]. However, there is the advantage of generating less joint particular rating of perceived exertion and pain immediately after training [31] and providing results in 6 weeks [32–34] compared to 8 weeks, the training duration commonly needed in HIRE [35].

Despite being a promising alternative, there is still no ideal protocol for applying the BFR in patients with knee OA. Thus, there is still lack of information about the most efficient and safety levels of pressure applied by the cuff to restrict blood flow and on the combination or not of the BFR with other therapeutic modalities [36]. Positive results for muscle strength improvement have been found using the BFR with 40 to 90% of the total arterial limb occlusion pressure (LOP) [37], associated with resistance exercises using low loads that vary between 10 and 30% of 1 RM [25]. Yet, no study has assessed whether BFR at rest could also promote similar gains in muscle strength for the knee OA treatment, which theoretically would increase adherence to knee OA treatment by patients, for minimizing the physical discomfort commonly presented in high and moderate-intensity exercises [31].

Therefore, the aim of this research is to assess whether different protocols of BFR are non-inferior to HIRE with placebo BFR for pain reduction in patients with knee OA.

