### Adverse event reporting and harms

During the trial, we will collect and record possible adverse events, describing the date of onset and date of resolution, evaluating event severity, investigating potential causal relationships with the intervention or with other suspect drugs, and assessing the potential effect of the event.

Some adverse events that may occur with BFR include rhabdomyolysis, subcutaneous hemorrhage, numbness, cold feeling, deep vein thrombosis, and itching [81, 82]. Severity must be defined according to the following criteria:
Mild: Awareness of signs or symptoms, but easily tolerable;Moderate: enough discomfort to interfere with normal daily activities;Severe: inability to perform normal daily activities;Threat to life: immediate risk of death due to the reaction that occurred;

All adverse events will be tracked until the incident is resolved or the trial is completed.

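### Chi-square tests are the only stated between-group comparison of adverse events; with 33 per arm they suit uncommon events poorly and, read as a five-arm test, do not target the contrasts of interest

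*Protocol article*

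**What the plan says.** The Statistical analysis section of the protocol article gives one sentence on comparing harms: "Chi-square tests will be used to test for possible differences in the adverse events observed between groups". It does not say whether this is a single test across all five arms or a set of pairwise tests, or whether events or participants are counted.

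The section on adverse event reporting lists what may occur: "Some adverse events that may occur with BFR include rhabdomyolysis, subcutaneous hemorrhage, numbness, cold feeling, deep vein thrombosis, and itching". It also provides for dates of onset and resolution, severity grading, assessment of causality, and follow-up until resolution or the end of the trial.

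The Sample size calculation section says "we will need 33 participants per group, resulting in a total sample of 165 participants". That number is derived from the WOMAC pain margin, and no event rate or power for harms is given. The Background treats cuff pressure as unsettled, including its safety: "there is still lack of information about the most efficient and safety levels of pressure applied by the cuff".

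**The concern.** The article fixes a method here rather than leaving it open, and the method fits the likely data poorly. The Pearson chi-square relies on a large-sample approximation, while several of the listed events would be expected in very few participants per arm. A test across five arms spreads its 4 degrees of freedom over every pattern of difference. The useful questions are narrower: does restriction add harm compared with HIRE, and does 80% pressure add harm compared with 40%?

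The comparison matters because the section on discontinuing interventions calls them known to be safe, on a cited source, and plans no interim analyses and no external data monitoring committee. The final between-arm comparison is then the main randomised evidence on harm that this trial can give. A p-value from an insensitive test would not show readers how large an excess the data leave possible.

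**Working it through.** **Inputs from the protocol article.** Five arms allocated equally, 33 per arm, 165 in total; two-sided 5% level; 15% drop-out, so about 33 × 0.85 = 28 completers per arm. No figure for harms is stated, so there is none to reproduce. The 33 itself comes from the pain calculation: 2 × 3.14² × (1.645 + 0.842)² / 2.1² = 27.7, rounded up to 28, and 28/0.85 = 32.9, rounded up to 33. This match uses a one-sided 5% level, which is a separate matter.

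**Assumed.** Event rates, since none is given, and a count of participants with at least one event.

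**Expected counts.** An expected 5 events in an arm of 33 needs an overall incidence of 5/33 = 15.2%. With 5% in three arms and 20% in two, the expected count is 33 × (3 × 0.05 + 2 × 0.20)/5 = 3.6.

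**Type I error, five-arm reading.** The statistic is the sum over arms of (x − n·p̂)² / (n·p̂·(1 − p̂)), compared with the 95% point of chi-square on 4 df. Simulation with n = 33 and the same true rate in every arm rejects about 0.6% of the time at a 1% rate and 1.6% to 1.7% (between runs) at 2%. The level is close to nominal by a 10% rate, so the shortfall concerns uncommon events.

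**Probability of missing a fourfold excess, five-arm reading, 33 per arm** (100,000 simulated trials per cell):

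| Baseline → raised rate | Excess in both 80% arms | Excess in one arm | Excess in all four BFR arms |
|---|---|---|---|
| 1% → 4% | 93% | 94% | 96% |
| 2% → 8% | 79% | 83% | 90% |
| 2.5% → 10% | 70% | 76% | 87% |
| 5% → 20% | 34% | 45% | 69% |
| 7.5% → 30% | 12% | 24% | 41% |
| 10% → 40% | 3% | 10% | 18% |

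With 28 per arm, the 5% → 20% row becomes 43%, 54% and 75%.

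**Pairwise reading.** For one arm against another (33 versus 33), Pearson chi-square has 49% power at 5% versus 20%, 29% at 5% versus 15%, and 15% at 2% versus 8%. Pairwise tests do not remove the problem.

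**Targeted contrasts with Fisher's exact test** (power by enumeration, full enrolment):

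| Contrast and rates | Exact test | Five-arm chi-square, same rates |
|---|---|---|
| Pooled BFR vs HIRE (132 vs 33), 20% vs 5% | 57% | 31% |
| 80% vs 40% pressure (66 vs 66), 20% vs 5% | 69% | 66% |
| 80% vs 40% pressure, 15% vs 5% | 37% | 37% |
| 80% vs 40% pressure, 10% vs 2% | 33% | 35% |

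In the pressure rows, the higher rate applies to both 80% arms and the lower rate to the other three. An uncorrected Pearson test would show 77% for 66 versus 66 at 20% versus 5%. However, the same kind of test on 132 versus 33 rejects about 9% of the time under the null at a 1% rate, so the exact test is the safer choice. A single BFR arm against HIRE (33 versus 33, 20% versus 5%) has only 29% exact power.

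**What an interval shows.** With zero events among n participants, the two-sided 95% upper limit is 1 − 0.025^(1/n): 10.6% for n = 33, 5.4% for n = 66 and 2.8% for n = 132.

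**The case against.** The strongest reply is that this is a condensed article about a trial sized for pain. Harms are not a stated hypothesis, low power for adverse events is normal, and table formats, intervals and sparse-cell handling usually sit in the full protocol or analysis plan. That stands as far as missing intervals go: their absence alone is no error. It does not cover the test that the article does name.

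Four stronger readings are tempting, and the documents do not support them:

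- **That a non-significant test will be reported as no difference, or as safety.** No section says so. The Statistical analysis section sets a margin only for BFR versus HIRE on WOMAC pain and reads its other comparisons as superiority comparisons. The description of the interventions as safe rests on a cited source, not on this test.
- **That a miss rate of 34% to 69% is a property of the plan.** It holds only for an assumed 5% versus 20% with all 33 per arm analysed.
- **That chi-square is the only way harms are judged.** Severity and causality are assessed for individual events. Rare serious events would be weighed case by case, and no test at this size could settle them. Chi-square is the only between-group comparison stated.
- **That the test must be a five-arm test.** The sentence is in the plural and fits pairwise tests as well.

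The gain from changing the test is also uneven, as the exact results for the pressure contrast show.

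**Conclusion.** The point holds in a limited form. The only stated between-group comparison of adverse events is a large-sample test applied to 33 per arm, where expected counts fall below 5 unless incidence is about 15% or more. On the five-arm reading it is strongly conservative for events at 1% to 2%, and it targets neither BFR versus HIRE nor 80% versus 40% pressure, although safe cuff pressure is named as an open question.

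Any power statement depends on event rates that the article does not give. For a fourfold excess with 33 per arm, the miss rate runs from about 3% (baseline 10%, excess in both 80% arms) to 96% (baseline 1%, excess in all four BFR arms). A non-significant result would therefore be weak evidence of equal safety. This is a warning about interpretation, not a description of what the plan says it will do. The primary analysis is unaffected.

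**What to change.** Replace the chi-square sentence in the Statistical analysis section with wording to this effect:

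> For each adverse-event category, the number and proportion of participants with at least one event will be given per arm. Risk differences with 95% confidence intervals (score or exact method) will be given for all BFR arms pooled versus HIRE (132 versus 33), for 80% versus 40% pressure (66 versus 66), and for each BFR arm versus HIRE. Where a test is given, it will be exact. Harms will be interpreted from the confidence interval, and a non-significant test will not be taken as evidence of equal safety.

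The cost is this wording and a few extra table rows; no new data or participants are needed. The intervals will be wide and will show openly that the trial cannot exclude a moderate excess of harm. The pooled BFR contrast gains power; the pressure contrast gains mainly an estimate with its uncertainty.
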